### Statistical Methods and Power Calculations

By using StatCal of Epi INFO 2000 software package (Centers for Disease Control and Prevention, Atlanta, GA, USA), a sample size of 21 patients for each group (42 patients for the whole study) has been calculated to reach a confidence level of 95% with a power of 80%, supposing that the hospital stay for LC with H the conversion rate can be reduced from 35% to 3%.

Analysis of data is by intention-to-treat. It will be specified when and how any deviations from randomised allocation, false inclusions, or missing outcomes have been handled. Repeated measures of the outcome will be performed with complete case analyses, potentially excluding individuals with some follow-up data, Eventual missing outcomes will be imputed using baseline values or by assuming that all missing participants have the same risk as the observed participants in the control group.

Data are expressed as numbers (%) and means (SD). The results of the two groups in comparison are analyzed using the Pearson's chi-square test and Fisher exact test, as appropriate, for proportions in case of discrete data. Fisher exact test is used when the data are very unequally distributed among the cells of the table or the expected frequency of any cell is less than 5 or the total N is less than 50. For means in case of continuous numerical data, the independent samples T test and the Mann-Whitney U-test are used, respectively for data normally and non-normally distributed. The data are previously tested for normality by the Kolmogorov-Smirnov test. For multivariate analysis the stepwise logistic regression is applied. A *p*-value of < 0.005 is in any case considered to be statistically significant.

Forward selection has been used as variable selection method; it will include all the baseline variables and all baseline variables are assessed for imbalance. The final model only contain variables with a p-value less than 0.05. Imbalances of baseline variables are defined comparing the groups using t tests for continuous variables and χ^2 ^tests for categorical variables. The adjustments are based upon the stratified logrank test or analysis of covariance. [11-13]The primary outcome is the conversion rate. Secondary outcomes are: intra-operative and post-operative morbidity and mortality, operative time and intra-operative blood losses.

All the secondary outcomes, including morbidity and mortality, operative time and blood losses, will be controlled as well for imbalances, (i.e. age, previous comorbidities, anticoagulant therapies, previous abdominal surgery).

Inclusion criteria are:

• Adult patients (>18 years)

• Clinical (pain, fever > 37.5°C, WBC > 10.000/microL), and ultrasound evidence of cholecystitis

• ASA I-III patients

• Informed consent

• Less than 72 h from the onset

Exclusion criteria are:

• Informed consent refusal

• Choledocholithiasis

• Generalized peritonitis

• Previous abdominal surgical procedures

• Patients with an intra-operative findings of different pathology will be excluded from the study

• Apache II score > 10

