## Background

In the developmental stage of laparoscopic cholecystectomy it was considered 'unsafe' or 'technically difficult' to perform laparoscopic cholecystectomy for acute cholecystitis [1,2].

With increasing experience in laparoscopic surgery, a number of centers have reported on the use of laparoscopic cholecystectomy for acute cholecystitis, suggesting that it is technically feasible but at the expense of a high conversion rate, which can be up to 35 per cent [3,4] and common bile duct lesions [5].

The HARMONIC SCALPEL^® ^(H) is the leading ultrasonic cutting and coagulating surgical device, offering surgeons important benefits including: minimal lateral thermal tissue damage, minimal charring and desiccation.

H technology reduces the need for ligatures with simultaneous cutting and coagulation: moreover there is not electricity to or through the patient

H has a greater precision near vital structures and it produces minimal smoke with improved visibility in the surgical field. [6]

In retrospective series LC performed with H was demonstrated feasible and effective with minimal operating time and blood loss: it was reported also a low conversion rate (3.9%). [6]

However there are not prospective randomized controlled trials showing the advantages of H compared to Monopolar Diathermy (MD – the most commonly used electrical scalpel) in LC.

Aim of this RCT is to demonstrate that H can decrease conversion rate compared to MD in LC for AC, without a significant increase of morbidity.

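### The 80% power claimed for 42 patients does not match the test the plan prescribes: two-sided Fisher at 0.05 gives 73% at the design rates, and 68% with the protocol's own cited Harmonic rate

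*Protocol article*

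**What the plan says.** All of the following is in the Protocol article.

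- **Size and power.** Statistical Methods and Power Calculations gives "a sample size of 21 patients for each group (42 patients for the whole study"), chosen "to reach a confidence level of 95% with a power of 80"%. Sidedness is not stated.
- **Rates.** The supposition is worded "the hospital stay for LC with H the conversion rate can be reduced from 35% to 3"%. The mention of hospital stay is stray; the rates are conversion rates, and conversion is named in that section as the primary outcome.
- **Test.** Proportions are compared by Pearson chi-square or Fisher. Fisher is required if the table is very unequal, or if "the expected frequency of any cell is less than 5 or the total N is less than 50".
- **Threshold.** The same section declares significance only at p below 0.005, in all cases.
- **Evidence for the rates.** The Background reports "a high conversion rate, which can be up to 35 per cent" for laparoscopic surgery in acute cholecystitis. For the Harmonic device, from retrospective series, "it was reported also a low conversion rate (3.9"%).
- **Looks.** Data Collection plans a statistical examination every 3 months during recruitment, and stopping if a statistically significant advantage emerges in one group.

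**The concern.** The document fixes the sample size, the event rates, the power and the test, and these four do not fit together. The conditions for Fisher are joined by "or", so a planned total of 42 settles the choice before any data exist. Fisher's exact test is conservative in small samples, so a sample size from a large-sample formula will generally fall short of its nominal power.

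The two rates also sit at the favourable edge of the protocol's own evidence. The control rate equals a stated upper limit, and the Harmonic rate is below the only Harmonic figure cited. Power at this size is steep in both.

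The 80% figure is the only justification given for 42 patients. If it is overstated, the ethics committee and later readers will understate the chance that a real reduction in conversions is missed, and may take a null result as stronger evidence than it is.

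**Working it through.** **Inputs.** n = 21 per arm, 1:1; MD rate 0.35, Harmonic rate 0.03, power 80%, confidence 95% (Statistical Methods and Power Calculations); cited Harmonic rate 0.039 and control rate of at most 0.35 (Background). Assumption: two-sided testing, with z = 1.960 and 0.842.

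**Step 1: the plan's own figure.**
- Unpooled: n = (1.960 + 0.842)² × (0.35×0.65 + 0.03×0.97) / 0.32² = 19.7, so 20 per arm. Power at 21 by this formula is 82.5%.
- Pooled variance under the null: n = 22.4, so 23 per arm.
- Pooled with continuity correction: 29 per arm.

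The stated 21 is within one patient per arm of the unpooled result. The uncorrected Pearson test has exact power of 84.0% at 21 per arm. So 21 is consistent with an uncorrected large-sample calculation.

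**Step 2: which test applies.** 42 < 50, so Fisher is required. Expected conversions per arm at the design rates are 21 × (0.35 + 0.03)/2 = 3.99, below 5, so a second condition is also met.

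**Step 3: exact Fisher power.** Sum the binomial probabilities of all 22 × 22 tables with two-sided Fisher p < 0.05. Nearly all the power comes from four rows:

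| Harmonic conversions | Probability at 3% | MD conversions needed | Probability at 35% | Product |
|---|---|---|---|---|
| 0 | 0.5275 | 5 or more | 0.9076 | 0.4788 |
| 1 | 0.3426 | 7 or more | 0.6433 | 0.2204 |
| 2 | 0.1060 | 9 or more | 0.2941 | 0.0312 |
| 3 | 0.0208 | 10 or more | 0.1623 | 0.0034 |

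These add to 0.7338; the remaining tables contribute almost nothing. Power is **73.4%**, which is 6.6 points below 80%. Fisher's maximum true type I error at this size is 2.3%.

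**Step 4: sensitivity to the rates and the threshold** (21 per arm). Control rates of 30%, 25% and 20% are assumed values inside the cited range.

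| MD v Harmonic | Fisher, 0.05 | Fisher, 0.005 | Boschloo, 0.05 |
|---|---|---|---|
| 35% v 3% | 73.4% | 30.4% | 80.8% |
| 35% v 3.9% | 68.2% | 26.6% | 77.0% |
| 30% v 3.9% | 53.9% | 14.7% | 63.1% |
| 25% v 3.9% | 37.8% | 6.4% | 45.6% |
| 20% v 3.9% | 22.2% | 2.0% | 27.2% |

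The Boschloo region orders tables by Fisher's p and maximises the error over a common rate on a 999-point grid. Its maximum size is 4.8% for one analysis.

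**Step 5: size needed under Fisher at 0.05.** For 35% v 3%, 24 per arm (48 in total) gives 81.3%. For 35% v 3.9%, 29 per arm (58 in total) gives 81.7%.

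**The case against.** **The number 21 is defensible.** This stands. A reader might infer that 21 is an arithmetic error that no standard formula gives. The unpooled formula gives 20, so the documents do not support that. What fails is the link between the formula and the prescribed test.

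**A one-sided reading would rescue the claim.** One-sided Fisher at 0.05 has 80.8% power at 21 per arm. But the protocol nowhere states a one-sided test.

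**The input rates are partly judgement.** This stands in part. 35% is at the cited limit, not above it. Moving from 3% to 3.9% changes the expected Harmonic conversions only from 0.63 to 0.82 in 21 patients and costs about 5 points of power. The Background does not say that the 3.9% series was confined to acute cholecystitis. The steeper losses rest on control rates assumed here. A reader might infer that the trial has a poor chance of detecting its target effect; at 0.05 and the design rates, 73% does not support that.

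**Changing the test would solve it at no cost.** A reader might infer that Boschloo's test restores 80% with type I error held at 5%. It does so only at 35% v 3%; with the cited 3.9% it gives 77%. The 5% bound holds for one final analysis, whereas Data Collection plans repeated looks with stopping on significance. At the analysis threshold of 0.005, Boschloo gives only 44.9% at 35% v 3%.

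**Conclusion.** The stated 80% power is wrong for the analysis the plan prescribes. Under two-sided Fisher at 0.05 it is 73.4% at the design rates, a type II error of about 27% instead of 20%, and 68.2% with the cited Harmonic rate. The direction and size of the shortfall at the design rates need no outside figure. They rest on two-sided testing, a single final analysis and all 42 patients analysed.

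Beyond that, power depends heavily on how far the true control rate lies below the cited ceiling, which the documents do not settle; the range shown is 22.2% to 53.9% for assumed rates of 20% to 30%. These figures at 0.05 are the lenient case. If the 0.005 threshold is meant as written, Fisher power is 30.4% even at 35% v 3%.

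**What to change.** 1. **Reconcile the threshold first.** The sizing uses 0.05 and the analysis 0.005. State one value and that the test is two-sided. Every power figure depends on this.
2. **Restate power for the test used.** If Fisher at two-sided 0.05 is kept with 42 patients, print 73% for 35% v 3% and 68% for 35% v 3.9%. Describe 35% as the upper end of the cited range, and add a short table for lower control rates, for example 20% to 30%.
3. **Optionally, name one primary test.** Boschloo's exact test at two-sided 0.05 would give 81% and 77% for the same two contrasts with no extra patients. Its 4.8% maximum size applies to a single final analysis, so the interim looks need their own error control whichever test is chosen.
4. **Or enlarge the trial.** At 0.05, Fisher reaches 80% with 48 patients in total for 35% v 3%, or 58 for 35% v 3.9%. At 58 the total is no longer below 50, and expected conversions are 29 × (0.35 + 0.039)/2 = 5.64 per arm, so the present rule would not necessarily select Fisher; the test would have to be named outright.
5. **Delete the stray mention of hospital stay** from the sample size sentence.

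Items 1, 2 and 5 cost only wording, and a less favourable power statement. Item 3 adds a less familiar but standard test. Item 4 costs 6 or 16 further patients.

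### The missing-data rules cannot be followed together: complete-case analysis conflicts with intention-to-treat and with imputation, and baseline-value imputation has nothing to act on for the main outcomes

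*Protocol article*

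**What the plan says.** All the rules stand together in the protocol article, section Statistical Methods and Power Calculations.

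- Analysis principle: "Analysis of data is by intention-to-treat".
- Reporting: "It will be specified when and how any deviations from randomised allocation, false inclusions, or missing outcomes have been handled".
- Repeated measures: "Repeated measures of the outcome will be performed with complete case analyses, potentially excluding individuals with some follow-up data".
- Imputation, joined to the previous rule by a comma: "Eventual missing outcomes will be imputed using baseline values or by assuming that all missing participants have the same risk". The risk meant is the one seen in control patients whose outcome is known.
- Primary outcome: "The primary outcome is the conversion rate".
- List of further outcomes: "Secondary outcomes are: intra-operative and post-operative morbidity and mortality, operative time and intra-operative blood losses".

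No text assigns either imputation rule to an outcome or says how the complete-case rule and the imputation rule divide the work. The end of the Data Collection section adds hospital stay, postoperative pain and return to normal activity as endpoints, and sets times for recording complications that run to 6 months.

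**The concern.** Three features look wrong.

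1. Intention-to-treat keeps every randomised patient in the comparison. The complete-case rule concedes that it may remove patients who have supplied data, and the next clause fills in what is missing. Both cannot apply to the same missed visit.
2. A baseline value can stand in only for a quantity that was measured before treatment. The named primary and secondary outcomes are not of that kind.
3. Giving missing patients in both arms the control-group risk pulls the arms together. For a superiority claim this errs on the safe side. For a claim that morbidity does not rise, it errs on the unsafe side, and the aim in the Background section makes both claims.

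With 21 patients per arm, each patient is 1/21 = 4.8% of an arm, so a few missed late visits carry weight in the follow-up comparisons.

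**Working it through.** **The plan's own figure.** Inputs from Statistical Methods and Power Calculations: conversion 35% v 3%, 95% confidence, 80% power, 21 per group. Two-sided testing is assumed because sidedness is not stated.

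- Unpooled variance: n = (1.960 + 0.842)² × (0.35×0.65 + 0.03×0.97) / 0.32² = 19.7, so 20 per arm.
- Pooled variance, no continuity correction: 23 per arm.

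The stated 21 lies between these. It is reproduced closely enough, and the point does not depend on it.

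**Can the rules be applied together?** There are two ways to read them.

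- Both rules apply to the same outcome. A patient with a missed visit is then excluded as incomplete and also imputed, which is impossible.
- Complete-case analysis applies to repeated measures and imputation to everything else. The only outcomes that could have a baseline value are those measured before and after surgery. These are repeated measures, so they have already gone to the complete-case rule, and baseline imputation has nothing left to act on. The conflict between complete-case analysis and intention-to-treat remains.

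**Is there a baseline value?**

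| Outcome | When it arises | Baseline of the same quantity |
|---|---|---|
| Conversion | in theatre | none |
| Operative time, blood loss | in theatre | none |
| Morbidity, mortality | during or after surgery | none |
| Hospital stay, return to activity | after surgery | none listed |
| Pain (VAS) | postoperative notes | none listed |

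The pre-operative items in Data Collection do not include a VAS score. If one were taken, carrying it forward would record an operated patient as unimproved. The resulting bias in an arm's mean is (missing fraction) × (baseline mean − follow-up mean). Purely as an illustration, assume 3 of 21 missing in one arm and none in the other, with VAS 7 before surgery and 3 after: (3/21) × (7 − 3) = 0.57 points of spurious difference.

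**Effect of control-risk imputation on conversion.** Let d be the missing fraction, equal in both arms and unrelated to outcome. The article gives no rate, so 5%, 10% and 20% are assumptions (about 1, 2 and 4 of 21 patients).

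- Control arm: (1 − d)×0.35 + d×0.35 = 0.35, unchanged.
- Harmonic arm: (1 − d)×0.03 + d×0.35. At d = 0.10 this is 0.027 + 0.035 = 0.062.
- Difference: (1 − d)×0.32.

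| d | Harmonic rate after imputation | Difference (points) | Power, control-risk | Power, complete cases (difference stays 32) |
|---|---|---|---|---|
| 0 | 3.0% | 32.0 | 77% | 77% |
| 5% | 4.6% | 30.4 | 71% | 75% |
| 10% | 6.2% | 28.8 | 65% | 73% |
| 20% | 9.4% | 25.6 | 52% | 67% |

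Power is by normal approximation at 21 per arm and two-sided 5%. It falls under control-risk imputation because the expected difference shrinks.

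**If baseline were read as not converted.** At d = 10% the rates become 0.9×35% = 31.5% and 0.9×3% = 2.7%. The difference is again 28.8 points, and both rates are understated.

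**Morbidity.** The article gives no morbidity rate, so only the algebra is available. If the true risk is higher with Harmonic by Δ, control-risk imputation leaves (1 − d)Δ. An increase is diluted by the same factor that dilutes a benefit.

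**The case against.** The strongest defence has four parts.

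- **Outcome type sorts the rules.** A risk can be assigned only to a binary outcome, and a baseline only to something measured beforehand, so the two imputation rules hardly compete. This largely stands. A reader might infer that the analyst is free to pick a rule after seeing the data and that the choice can decide the direction of the result. The documents do not support that. Control-risk imputation gives (1 − d)(pC − pH), where pC and pH are the control and Harmonic conversion risks. This shrinks but cannot change sign, and nothing shows the two rules giving opposite answers on one outcome.
- **Imputation is compatible with intention-to-treat.** This stands in full. A reader might infer that all three rules breach the principle, but imputation keeps randomised patients in. Only the complete-case clause is in conflict. Nor does control-risk imputation produce wrong values as such. For most outcomes here the baseline value is undefined rather than wrong.
- **The pain example rests on a score the article does not list**, and the dated follow-up visits are stated for complications, not pain. This stands, so the 0.57 is only an illustration. A reader might also infer that this example shows an understated standard error. It shows the reverse. With an assumed SD of 2, the mixture variance is 4 + (3/21)(18/21)(16) = 5.96 and the SD is 2.44. The standard error is 2.44/√21 = 0.53, against 2/√18 = 0.47 for the 18 observed patients.
- **Detail by outcome belongs in an analysis plan that is not shown, and the theatre outcomes will rarely be missing.** The second half stands and limits the weight of the point. The first half does not answer it: these are rules the article states and that conflict, not detail it leaves out.

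**Conclusion.** The point holds in a limited form and should be corrected. The complete-case rule conflicts with the declared intention-to-treat analysis and with the imputation rule beside it. Baseline-value imputation cannot be carried out for any named primary or secondary outcome. Control-risk imputation is defensible for conversion, where it costs 3.2 of 32 points at an assumed 10% missing. It is not safe as the sole basis for concluding that morbidity has not increased.

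The sizes rest on assumed missing rates, equal in both arms and unrelated to outcome, and on the planning rates of 35% and 3%. The practical exposure is in complications to 6 months, pain and return to activity. The primary comparison is little affected if conversion is recorded for nearly everyone, as should be the case for an event in theatre.

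**What to change.** - Delete imputation by baseline value.
- Replace complete-case analysis of any repeated measure with a method that uses all available observations from every randomised patient, for example a likelihood-based mixed model. State which outcomes are measured repeatedly, since the article gives no schedule for pain.
- For each binary outcome, name one primary handling of missing values in advance. Restricting to patients with an observed outcome is itself a complete-case analysis. If that is chosen, say so and do not present it as the cure for the present rule.
- Report control-risk imputation and best-case/worst-case by arm as labelled sensitivity analyses.
- Do not rest the morbidity conclusion on control-risk imputation alone.

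The cost is a change of wording and a little more analysis work. No additional patients are needed.

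### Outcomes judged non-normal are to be summarised as mean (SD) but tested by Mann-Whitney, so the p-value does not test the difference in means that is printed

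*Protocol article*

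**What the plan says.** All of the rules are in the Statistical Methods and Power Calculations section of the protocol article.

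- Summary: "Data are expressed as numbers (%) and means (SD"). No median, interquartile range or rank-based estimate is named anywhere in the article.
- Test: "For means in case of continuous numerical data, the independent samples T test and the Mann-Whitney U-test are used". The first applies when the data look normal, the second when they do not.
- Selection: "The data are previously tested for normality by the Kolmogorov-Smirnov test".
- Threshold: a p "value of < 0.005 is in any case considered to be statistically significant".
- Size: "a sample size of 21 patients for each group (42 patients for the whole study) has been calculated".

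Operative time and blood loss are secondary outcomes in the same section. Hospital stay and postoperative pain are in the endpoint list of the Data Collection section, which also says that pain is scored by VAS.

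**The concern.** The normality check changes the test but not the summary. The t test and mean (SD) belong together. Mann-Whitney and mean (SD) do not: the test asks whether patients in one arm tend to have lower values than patients in the other, and it gives an extreme value no more weight than its rank. The mean and SD give that value full weight.

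The mismatch therefore arises exactly where the data were judged unsuitable for a mean-based test. A reader of the results table would take the p-value as evidence about the two means beside it, and would have no size of effect that matches the test. At 21 per arm, one complicated patient can move a mean a long way, so operative time, blood loss, stay and pain could all be misread.

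**Working it through.** **Arm size.** This point disputes no stated figure; 21 per arm is used only as the setting. It is roughly reproduced from the stated inputs (35% v 3%, 95% confidence taken as two-sided, 80% power) by the unpooled normal formula: n = (1.96 + 0.842)² × (0.35×0.65 + 0.03×0.97) / 0.32² = 7.849 × 0.2566 / 0.1024 = 19.7, so 20 per arm. The pooled version gives 23.

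**Can the means and the ranks disagree at this size?** Constructed stays in days, 21 per arm (assumed data):

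- H: ten of 2, nine of 3, one of 4, one of 40. Sum = 20 + 27 + 4 + 40 = 91; mean = 91/21 = 4.33; SD 8.19; median 3.
- MD: eight of 3, nine of 4, four of 5. Sum = 24 + 36 + 20 = 80; mean = 80/21 = 3.81; SD 0.75; median 4.

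The printed means favour MD by 0.52 days. For the ranks, compare all 21 × 21 = 441 pairs:

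- H shorter: 10×21 + 9×13 + 1×4 = 331
- tied: 9×8 + 1×9 = 81
- H longer: 1×8 + 1×21 = 29

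The probability that H is shorter, counting ties as half, is (331 + 40.5)/441 = 0.84. Mann-Whitney gives p = 0.00007 in favour of H, the Hodges-Lehmann difference is -1 day, and the t test gives p = 0.77. Kolmogorov-Smirnov in the H arm gives D = 0.469, p = 0.00009, so the plan's rule, if applied by arm, selects Mann-Whitney.

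The reversal rests on one patient. Without the 40-day stay, the H mean is 51/20 = 2.55. The means reverse only if that stay exceeds 80 - 51 = 29 days; at 25 days they are 76/21 = 3.62 v 3.81 and agree with the ranks.

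**How often would a reversal occur?** Simulation with assumed inputs: 21 per arm, lognormal stays with medians 2.5 (H) and 3.5 (MD) days, and 5%, 10% or 15% of patients in both arms staying 10-25 days longer. The share is of significant Mann-Whitney results in which the means point the other way.

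| Log SD | Significant at p<0.05 | Significant at p<0.005 |
|---|---|---|
| 0.3 | up to about 15% | about 3-5% |
| 0.4 | about 5-8% | about 0.5-1.4% |
| 0.5 | down to about 2% | below 1% |

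Without added long stays there were essentially none at these SDs. Two further checks:

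- Pure lognormal shifts with log SD 0.5-1.5: a reversal with p<0.05 in 0-0.9% of all trials.
- Typical stay 4 (MD) v 3 (H) days, 5% long stays on MD and 5%, 10% or 15% on H: a reversal in 4.7%, 8.9% and 9.6% of all trials with p<0.05, and in 0.5-0.8% with p<0.005.

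**Other outcomes.** Constructed sets of 21 per arm, MD v H, with Mann-Whitney favouring H in both:

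- Blood loss: means 54.3 v 67.6, p = 0.00001. This needs two H patients at 400 and 500.
- Pain, 0-10 scale: means 3.29 v 3.62, p = 0.0027. This needs five of the 21 H patients at 9 or 10.

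**The case against.** The strongest reply is that this is reporting detail. The article condenses a fuller protocol and the analysis plan is not shown; table summaries and interval estimates are commonly left to those documents. The summary sentence does not forbid medians. That stands as far as a missing Hodges-Lehmann estimate goes: its absence alone would be no finding. It does not remove the point, because the article states both halves itself, a mean-based summary for continuous data and a rank test described as comparing means, and the two do not fit.

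A second reply is that the section also names analysis of covariance, and that secondary outcomes are to be controlled for imbalances. That would give an adjusted mean difference with its own p-value. It helps in part, but it is described as an adjustment for baseline imbalance and does not change what the Mann-Whitney p-value tests.

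A reader might also infer that the report is likely to show means and p-values in opposite directions for stay, blood loss and pain. The documents do not support that. They give no distributions, and they leave non-normality to the pre-test. Ordinary skew almost never produces a significant reversal; it takes a few extreme values in the arm that is otherwise lower. A VAS is bounded, which limits outliers further. A reader who sees 4.3 (8.2) beside 3.8 (0.7) would also suspect an outlier.

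**Conclusion.** The mismatch is real and follows from the article's own wording: whenever Mann-Whitney is selected, the printed difference in means is not the quantity tested. The usual harm is a mean (SD) that describes skewed data poorly beside a p-value about something else. A reversal of direction is possible but uncommon: about 2-15% of results significant at p<0.05 and about 0.3-5% at the plan's p<0.005, under the equal-contamination model with log SD 0.3-0.5. At the lower end so few reversals occur that repeated runs range from 0 to 0.6%. Every distribution behind these figures is assumed.

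Severity is low. Conversion, the primary outcome in the Statistical Methods section, is binary and untouched, and the sample size does not change. Both thresholds are shown because the sizing uses 95% confidence and the analysis uses 0.005; that difference is a separate matter.

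**What to change.** In the Statistical Methods section:

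1. Remove the words *for means* as they apply to Mann-Whitney.
2. Replace the single summary rule with: *Outcomes analysed by Mann-Whitney are summarised as median (interquartile range), with the Hodges-Lehmann difference and its 95% confidence interval. Outcomes analysed by the t test are summarised as mean (SD), with the difference in means and its 95% confidence interval.*
3. If mean bed-days are also wanted, give the mean difference with its own bootstrap or permutation interval, not the Mann-Whitney p-value.

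In the constructed stay example the table would then show medians 3 v 4 and a shift of -1 day beside p = 0.00007, so estimate and test agree. The cost is two sentences and different table columns. No new data are needed, and no sample size or power figure changes.

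### The trial is sized at a 5% significance level but significance is declared only at p < 0.005; with the required Fisher test, power is about 73% at 0.05 and about 30% at 0.005, not 80%

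*Protocol article*

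**What the plan says.** All the conflicting statements are in the Protocol article, Statistical Methods and Power Calculations.

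- **Sample size.** The 21 patients per group (42 in all) are calculated "to reach a confidence level of 95% with a power of 80" per cent, on the supposition that "the conversion rate can be reduced from 35% to 3" per cent.
- **Outcome.** "The primary outcome is the conversion rate".
- **Test.** Proportions are compared by Pearson's chi-square or Fisher's exact test. Fisher is used, among other conditions, when "the expected frequency of any cell is less than 5 or the total N is less than 50".
- **Decision rule.** A p-value "< 0.005 is in any case considered to be statistically significant".
- **The only other p-value criterion.** "The final model only contain variables with a p-value less than 0.05". This governs which variables stay in the regression model, not whether a treatment comparison is significant.

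The closing part of Data Collection adds statistical examinations every 3 months during inclusion and says that the study stops if a statistically significant advantage appears in one group. It does not mention 0.005.

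**The concern.** A 95% confidence level corresponds to a significance level of 0.05. The decision rule is ten times stricter and, by its own wording, makes no exception for the primary outcome. A sample size calculated at one level does not deliver its stated power at the other.

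The threshold decides whether the trial is reported as positive. Results between 0.005 and 0.05 are quite likely under the design assumptions. For such a result, one sentence of the article supports calling it significant and another supports calling it non-significant. If the choice is made once the data are known, the success criterion is no longer prespecified in any useful sense.

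**Working it through.** **Inputs, all from Statistical Methods and Power Calculations.** Conversion 35% (MD) and 3% (H); 21 per arm; power 80%; level 0.05 for sizing and 0.005 for the decision. Sidedness is not stated. Two-sided is assumed, and one-sided results are given as a check.

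**1. Reproduce the stated size.** The difference is 0.35 − 0.03 = 0.32, squared 0.1024. The sum of variances is 0.35 × 0.65 + 0.03 × 0.97 = 0.2275 + 0.0291 = 0.2566. The mean rate is 0.19.

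- Unpooled: n = (z_α + z_β)² × 0.2566 / 0.1024. At 0.05, (1.960 + 0.842)² × 0.2566 / 0.1024 = 19.7, so 20 per arm.
- Pooled: n = [z_α √(2 × 0.19 × 0.81) + z_β √0.2566]² / 0.1024. At 0.05 this is 22.4, so 23 per arm.

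The stated 21 lies between the two, so it fits a level of 0.05. With z_α = 2.807 for 0.005, the same formulas give 33.4 and 38.4, so 34 and 39 per arm. The stated size was not calculated at 0.005.

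**2. Which test applies.** Total N is 42, below 50. Expected conversions are 21 × 0.19 = 3.99 per arm, below 5. Either condition alone requires Fisher's exact test.

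**3. Power with 21 per arm, 35% vs 3%.** The exact figures sum the probabilities of all pairs of outcomes from two Binomial(21) arms whose p-value falls below the threshold.

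| Method | p < 0.05 | p < 0.005 |
|---|---|---|
| **Fisher, two-sided (required test)** | **73.4%** | **30.4%** |
| Fisher, one-sided | 80.8% | 44.9% |
| Pearson chi-square, exact enumeration | 83.9% | 44.9% |
| Normal approximation, pooled, two-sided | 77.3% | 42.9% |
| Normal approximation, unpooled, two-sided | 82.5% | 53.5% |
| Normal approximation, unpooled, one-sided | 89.4% | 62.5% |

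The normal approximations are without continuity correction; with it, the pooled two-sided figure at 0.005 is 27.1%. The highest value found at 0.005 is 62.5%, so no variant comes near 80%.

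**4. Separate the two causes.** From the stated 80% to 73.4% is 6.6 percentage points, due to Fisher's test. From 73.4% to 30.4% is 43.0 points, due to the threshold.

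**5. What the rule means in patients.** Two-sided Fisher p-values, 21 per arm:

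| MD conversions | H conversions | p |
|---|---|---|
| 5 | 0 | 0.048 |
| 7 | 1 | 0.045 |
| 7 | 0 | 0.0086 |
| 8 | 0 | 0.0034 |
| 9 | 1 | 0.0089 |
| 10 | 1 | 0.0036 |

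The design rates correspond to about 7 vs 1 (21 × 0.35 = 7.35; 21 × 0.03 = 0.63). That result is significant at 0.05 and not at 0.005. With no H conversions, the written rule needs 8/21 (38%) under MD, above the planning rate of 35%.

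**6. Size needed for 80% with two-sided Fisher.** At 0.05, 24 per arm (81.3%; 23 per arm gives 78.9%). At 0.005, 40 per arm (80.5%; 39 per arm gives 78.6%).

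**The case against.** **It is a misprint.** The sample size uses 95% confidence and the model-retention rule uses 0.05, so 0.005 could well be a slip. That is plausible, and it softens the practical consequence. But nothing in the article says so, the model-retention rule has a different purpose, and a slip in the success criterion still has to be corrected before analysis.

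**The stricter level protects against repeated looks or several endpoints.** The article does not connect 0.005 to its interim examinations, its stopping statement or its list of endpoints. Had that been the purpose, the sample size would have had to allow for it, and it does not.

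**The 30% depends on the method.** This is true. It is specific to the two-sided Fisher test; other methods give higher or lower figures, as tabulated. Sidedness is an assumption. The finding that power at 0.005 falls well short of 80% does not depend on these choices.

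**Stronger readings that the article does not support.** A reader might infer that the threshold alone takes power from 80% to 30%. It does not, because the Fisher rule already gives about 73% at 0.05. A reader might also infer that the trial is headed for a false negative, or that analysing at 0.05 would simply be a criterion changed after the fact. The first holds only if 0.005 is applied literally and the full planned effect is true. The second ignores that the sample-size sentence already gives 95% confidence.

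**Conclusion.** The contradiction stands. The article fixes two significance levels, and the stated 80% power does not hold for the required two-sided Fisher test at either. With 21 per arm and 35% vs 3%, power is about 73% at 0.05 and about 30% at 0.005. Applied literally, the rule would miss the full planned effect about 70% of the time (100% − 30.4% = 69.6%). Most of the shortfall comes from the threshold and a smaller part from the test.

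These figures rest on a two-sided test, the design rates being true, 21 analysed patients in each arm and a single analysis. At 0.05, a one-sided Fisher test would reach 80.8%, but the article does not specify one. Because the level decides the primary conclusion and the correction is textual, it should be settled before any outcome comparison.

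**What to change.** In Statistical Methods and Power Calculations:

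1. State one significance level for the primary comparison of conversion rates: two-sided 0.05, to match the basis of the sample size.
2. Restate the power as about 73% for the two-sided Fisher test with 21 per arm. Changing 0.005 to 0.05 alone would leave an incorrect 80% in place.
3. If 0.005 is really intended, say so, give the reason, and restate the power as about 30%.
4. Make the wording agree with the 3-monthly examinations and the stopping statement in Data Collection. Saying that the primary comparison is tested only once would contradict them as they stand.

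The cost is an amendment of a few sentences and a less favourable stated power; restating it needs no extra patients. If the sponsor wants to keep 80% with two-sided Fisher, the size becomes 24 per arm at 0.05 (48 in all, 6 more than planned) or 40 per arm at 0.005 (80 in all, 38 more), before any allowance for interim looks.
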